**Fig. 1 Fig1:**
[figure not shown]
FIBROTHERM timeline

### Sample size

The primary outcome is the modification of the FIQ total score, whose minimum clinically relevant difference is 14% as compared to its initial value (Burckhardt et al. 1991). We expect a decrease in the FIQ total score of at least 14% in the 30% of the control cohort and 45% in the BT cohort. A number of 217 patients per group allows estimating an absolute difference of 15% (45—30%) in the incidence of the primary outcome between the two cohorts at an alpha level = 0.05 and with a power of 90% (Pearson’s chi-squared test). Assuming a loss to follow-up of 20%, 260 (217 + 43) patients will be enrolled per group, for a total of 520 patients.

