### Statistical analysis plan

#### Primary outcome

The primary outcome of the study will be the difference in the proportion of patients with reduction in FIQ-Total score > 14% in the BT vs. the control cohort. As described above, Pearson’s chi-square test will be used to evaluate the statistical significance of this difference, considered clinically relevant if ≥ 15%, at an alpha = 0.05 level and with a power of 90%. Subsequently, a binomial regression model (BRM) will be used to quantify the size of this difference and its precision (95% confidence interval) (Long and Freese 2006). The response variable of the BRM will be the proportion of subjects with a reduction in the FIQ-Total score > 14% at 15 days, and the predictor will be the cohort (discrete: 0 = control cohort; 1 = BT cohort). The effect size estimated by the BRM will be expressed both as absolute and relative risk change. Marginal estimates with 95% confidence intervals of the percentages of patients with reduction in FIQ-Total score > 14% in the two cohorts will be calculated.

In the BT cohort, we will also use a BRM having as a response variable, the proportion of subjects with a reduction in the FIQ-Total score > 14% and time as predictor (discrete; 0 = 15 days; 1 = 45 days) to verify the stability of the change in the FIQ-Total score at 30 days. A Bonferroni correction will be used to correct the 95% confidence intervals and associated p-values. The univariable BRM described above for the evaluation of the primary outcome between the BT and control cohorts will subsequently be expanded to a multivariable model by adding predictors (= potential confounders) determined preliminarily with the clinicians participating in the study. An univariable selection of the predictors will not be made, but they will be progressively added to the model to verify the effect on the relative risk estimated by the model itself (Greenland and Pearce 2015). Interactions initially determined or suggested by the multivariable analysis may also be included among the predictors. It is possible, and indeed expected, that the BRM will have to be replaced by a Poisson regression model (PRM) with robust confidence intervals, to overcome the well-known problems of fitting a BRM with multiple predictors (Zou 2004; Lumley et al. 2006). At this stage, we will only model the relative risk because, being this a cohort study, the relative risk measure is expected to be more transferable than the absolute risk.

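### The 20% loss allowance was added to 217 instead of dividing by 0.8, so 260 per group leaves 208 evaluable and about 89% power, not 90%

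*Protocol article*

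**What the plan says.** The protocol article, Sample size, sets the assumed responder rates: "We expect a decrease in the FIQ total score of at least 14% in the 30% of the control cohort and 45% in the BT" group. It continues: "A number of 217 patients per group allows estimating an absolute difference of 15" percentage points, "at an alpha level = 0.05 and with a power of 90" per cent, using Pearson's chi-squared test. The attrition allowance follows directly: "Assuming a loss to follow-up of 20%, 260 (217 + 43) patients will be enrolled per group, for a total of 520 patients".

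The Statistical analysis plan section, under Primary outcome, names the same test ("Pearson’s chi-square test will be used to evaluate the statistical significance of this difference") and repeats the operating characteristics: "at an alpha = 0.05 level and with a power of 90" per cent.

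**The concern.** The breakdown 217 + 43 shows that the 20% was taken of the evaluable number and added to it. A loss to follow-up rate applies to the patients who enter the study, so the enrolled number should be the evaluable number divided by one minus the loss rate. Adding 20% always gives too few patients. If it was done here, the enrolment of 260, the loss of 20% and the power of 90% cannot all be true, and the power quoted for the primary comparison is overstated in both places where it appears.

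**Working it through.** **Inputs**, all from Sample size: control rate p0 = 0.30; BT rate p1 = 0.45; difference 0.15; alpha 0.05; power 0.90; equal groups; loss 20%; enrolment 260 per group. Sidedness is not stated, so two-sided is taken as an assumption. It is supported by step 1.

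**1. Reproduce the 217.** The pooled-variance formula for two proportions, with mean rate p = 0.375, is

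n = [1.960 × √(2p(1−p)) + 1.2816 × √(p0(1−p0) + p1(1−p1))]² / 0.15²

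- √(2 × 0.375 × 0.625) = √0.46875 = 0.6847
- √(0.21 + 0.2475) = √0.4575 = 0.6764
- n = (1.3419 + 0.8668)² / 0.0225 = 4.878 / 0.0225 = 216.8, so **217 per group**

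This matches the protocol. A one-sided test would give 177, and a two-sided test with continuity correction 230, so neither of those was used.

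**2. Reproduce the 260.** 0.20 × 217 = 43.4, printed as 43, and 217 + 43 = 260. The allowance is therefore n × (1 + 0.20).

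**3. Apply the stated loss to the stated enrolment.** 260 × 0.80 = **208 evaluable per group**, which is 9 fewer than 217 (9/217 = 4.1%). Put another way, 20% of 260 is 52, not 43.

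**4. Correct inflation.** 217 / 0.80 = 271.25, so **272 per group, 544 in total**. Planned enrolment is 12 per group short (12/272 = 4.4%), or 24 overall.

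**5. Power at 208 per group.**

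Power = Φ[(0.15 × √n − 1.3419) / 0.6764]

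| Evaluable per group | Normal approximation | Exact enumeration of Pearson chi-squared |
|---|---|---|
| 217 | 90.0% | 90.2% |
| 208 | 88.8% | 88.7% |

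For n = 208: (0.15 × 14.422 − 1.3419) / 0.6764 = 0.8214 / 0.6764 = 1.214, and Φ(1.214) = 0.888. The loss of power is 1.2 points by the approximation and 1.5 by exact calculation.

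**6. Loss that 260 can absorb.** 1 − 217/260 = 43/260 = **16.5%**.

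**The case against.** The strongest counter-argument is about weight. A drop from 90.0% to 88.8% would change no decision, and the study is not materially underpowered. That is right, and it limits how much should be made of the point. It does not make the printed figures consistent.

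Second, the 20% carries no time point. The primary outcome is measured at 15 days, whereas follow-up runs to a telephone visit at 45 days (Follow up). If 20% is the loss over the whole period, loss by day 15 could be 16.5% or less, and 90% power would then hold. This is possible, but Sample size makes no such distinction and applies the 20% directly to the number needed for the primary outcome.

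Third, the section on techniques common to primary and secondary outcomes plans multiple imputation when data can be taken as missing at random, so lost patients need not drop out of the analysis. However, that is conditional, and the sample size calculation does not use it: it treats lost patients as needing replacement.

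Finally, the restated power is also nominal. It applies to an unadjusted comparison of two equal groups, while the cohorts are formed by patients' own choice and the comparison is later expanded to a multivariable model. That stands, and the corrected sentence should say which test the power refers to.

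**Conclusion.** The point holds. The base figure of 217 is right; the attrition step is wrong, and the protocol's own breakdown shows how. Under the stated 20% loss, 260 enrolled per group yields 208 evaluable and about 89% power. The error is real but small: 9 evaluable patients per group, 12 enrolled per group, and 1.2 to 1.5 points of power. It should be corrected because it is a false figure in the primary sample size justification, not because the design fails.

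The conclusion rests on a two-sided test (the version that reproduces 217), equal groups, the 20% applying at the 15-day assessment, and lost patients not contributing to the chi-squared test.

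**What to change.** Keep the enrolment at 520 and replace the attrition sentence in Sample size with wording such as:

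> With 260 patients enrolled per group and a 20% loss by day 15, 208 per group will be evaluable, giving about 89% power for the unadjusted chi-squared test at two-sided alpha 0.05; 90% power is retained for losses of up to 16.5%.

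Under Primary outcome in the Statistical analysis plan section, change the repeated 90% to match, or refer back to Sample size. If the 20% was meant to cover the whole 45 days, say so and give the loss expected by day 15.

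The cost is one sentence in each of two sections and a slightly less favourable power figure, with no additional patients and no change to design or analysis. The alternative that preserves 90% power at 20% loss is 272 per group, or 24 more patients in total. For about one point of power that is hard to justify, particularly as Study design and ethics closes enrolment in November 2024.

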### Statistical analysis plan

#### Primary outcome

The primary outcome of the study will be the difference in the proportion of patients with reduction in FIQ-Total score > 14% in the BT vs. the control cohort. As described above, Pearson’s chi-square test will be used to evaluate the statistical significance of this difference, considered clinically relevant if ≥ 15%, at an alpha = 0.05 level and with a power of 90%. Subsequently, a binomial regression model (BRM) will be used to quantify the size of this difference and its precision (95% confidence interval) (Long and Freese 2006). The response variable of the BRM will be the proportion of subjects with a reduction in the FIQ-Total score > 14% at 15 days, and the predictor will be the cohort (discrete: 0 = control cohort; 1 = BT cohort). The effect size estimated by the BRM will be expressed both as absolute and relative risk change. Marginal estimates with 95% confidence intervals of the percentages of patients with reduction in FIQ-Total score > 14% in the two cohorts will be calculated.

In the BT cohort, we will also use a BRM having as a response variable, the proportion of subjects with a reduction in the FIQ-Total score > 14% and time as predictor (discrete; 0 = 15 days; 1 = 45 days) to verify the stability of the change in the FIQ-Total score at 30 days. A Bonferroni correction will be used to correct the 95% confidence intervals and associated p-values. The univariable BRM described above for the evaluation of the primary outcome between the BT and control cohorts will subsequently be expanded to a multivariable model by adding predictors (= potential confounders) determined preliminarily with the clinicians participating in the study. An univariable selection of the predictors will not be made, but they will be progressively added to the model to verify the effect on the relative risk estimated by the model itself (Greenland and Pearce 2015). Interactions initially determined or suggested by the multivariable analysis may also be included among the predictors. It is possible, and indeed expected, that the BRM will have to be replaced by a Poisson regression model (PRM) with robust confidence intervals, to overcome the well-known problems of fitting a BRM with multiple predictors (Zou 2004; Lumley et al. 2006). At this stage, we will only model the relative risk because, being this a cohort study, the relative risk measure is expected to be more transferable than the absolute risk.

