## Methods

### Study design and ethics

FIBROTHERM is a prospective multi-center, two-cohort observational study. The enrollment period will take place from April 2023 to November 2024 (deadline for the enrollment of the last patient) by the centers participating in the study. From June 2025, the data will be analyzed and then, disseminated. The estimated total duration of the study will be 26 months.

The study will be conducted in accordance with the “Declaration of Helsinki (1964) and following amendments. All eligible patients will provide a written informed consent, and this will be recorded in the appropriate outpatient file. The study protocol was approved by the Ethics Committee of the Area Vasta Sud Est-Toscana (Italy) on March 2023; the same document was submitted and approved by local Ethics Committees of the other participating centers to ensure that all local regulatory requirements were met. Furthermore, the study was registered on http://www.clinicaltrials.gov: NCT05801497.

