### Interventions and study arms

This study consists of two parallel cohorts:BT Cohort (BTC): Patients will receive a cycle of bath or of mud-bath therapy once daily for 12 days in addition to their usual treatments for FS (see below). The thermal treatment cycle will include one session per day for a total of two weeks, with a break between the fifth and seventh day to prevent the onset of a thermal crisis. This protocol aligns with current practices and is endorsed by the Italian National Health Service which covers a cycle of a 12-day treatments, once a year for patients with rheumatic diseases such as FS. The mineral thermal baths will be carried out in a single tub or in a pool, with a duration of 10 min at a temperature of 37–38° C. The thermal mud will be applied to the skin according to standardized methods, with a duration of 15–20 min, at temperatures ranging between 40–45° C. A rest period of about 20–30 min will follow BT treatment. The whole treatment duration will last 1 h, approximately. Only muds and baths belonging to the classes of sulfurous, bicarbonate, chloride-sodium, sulphate and arsenical-ferruginous waters—according to the classification of Marotta and Sica (1933), will be allowed.Control Cohort (SCC): This group will include patients who will refuse the BT for personal reasons. Patients will continue their established routinely care for FS.

The usual care treatment will correspond to pharmacological and non-pharmacological therapies as reported in EULAR guidelines (Macfarlane et al. 2016). The intervention program must have already been stabilized for at least 3 months before the start of the study. During the study period, the patient can modify the therapy if necessary; this change will be reported.

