BT also offers significant mental health benefits, particularly in reducing anxiety and depressive symptoms common in FS. Its anti-inflammatory effects may influence brain chemistry, as inflammation is linked to mood disorders like depression (Fioravanti et al. 2024, Koroglu and Yıldız 2024). Notably, IL-6, an inflammatory marker, is associated with sleep disturbances, and BT’s ability to regulate IL-6 could be a key mechanism behind its positive effects on sleep quality. In addition, warm, mineral-rich water promotes relaxation and reduces stress, contributing to better sleep patterns (Antonelli et al. 2024a, 2024b). This restorative sleep further enhances the benefits of BT by reducing fatigue and improving psychological resilience, ultimately leading to better overall well-being (Moini Jazani et al. 2023; Manica et al. 2024).

Furthermore, we expect to confirm a good tolerability of BT in a large sample of patients with moderate-severe FS.

In conclusion, the favorable effect of BT extended to several domains, including quality of life, anxiety and depression, could be particularly useful in the multimodal treatment of this disease.

A notable strength of this study is its large sample size and the involvement of nine specialized public facilities across Italy, which ensures a comprehensive representation of the national context.

Moreover, the results of this study have the potential to provide valuable insights that could help shape best practices for the clinical management of FS. Additionally, it may offer new evidence to further validate the role of BT as part of the complex approach to treating FS.

Nevertheless, there are some limitations to consider. Firstly, the observational nature of the study is a key limitation. Secondly, there will be no standardization of the BT treatments, as different mineral waters and specific protocols will be employed at each center, which is consistent with a real-world study design. Similarly, the routine care for FS, including both pharmacological and non-pharmacological treatments, will not be standardized but will follow the recommendations provided by the EULAR guidelines (Macfarlane et al. 2016).

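### The primary outcome is tested by an unadjusted chi-square between BT takers and BT refusers, and the planned adjusted model is not named as the basis for the conclusion

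*Protocol article*

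**What the plan says.** The design is non-randomised: "FIBROTHERM is a prospective multi-center, two-cohort observational study" (Study design and ethics). Under Interventions and study arms, the exposed cohort is described by "Patients will receive a cycle of bath or of mud-bath therapy once daily for 12 days in addition to their usual treatments for FS", and the control cohort by "This group will include patients who will refuse the BT for personal reasons". The aim at the end of the Introduction is causal: whether BT increases the share of patients who reach the MCID, compared with standard care.

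The Primary outcome part of the Statistical analysis plan sets this order:

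1. Pearson's "chi-square test will be used to evaluate the statistical significance of this difference, considered clinically relevant if ≥ 15" per cent, "at an alpha = 0.05 level and with a power of 90" per cent.
2. A binomial regression in which "the predictor will be the cohort (discrete: 0 = control cohort; 1 = BT cohort"), reported as absolute and relative change.
3. Later, a multivariable version. Its confounders are settled beforehand with the participating clinicians, there is no univariable selection, and predictors are added step by step to see how the relative risk moves. In addition, "Interactions initially determined or suggested by the multivariable analysis may also be included among the predictors". A robust Poisson model is expected to replace the binomial one. At this stage only the relative risk is modelled.

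The Sample size section rests on the same chi-square: 30% against 45%, with 217 per group, raised to 260.

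**The concern.** Cohort membership is the patient's own choice. People who accept a two-week spa course and people who decline it may differ in prognosis, and the outcome is a self-completed questionnaire. A crude chi-square tests whether two observed proportions are equal. It cannot separate an effect of BT from a difference that would have existed without BT.

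The plan nevertheless gives alpha and power to that crude test and to no other analysis. The criterion of clinical relevance is also tied to the crude result. It is an absolute difference of 15 percentage points, whereas the adjusted stage yields only a relative risk. As written, both decisions on the primary outcome, significance and relevance, rest on the unadjusted comparison. If crude and adjusted results disagree, the plan does not say which one answers the primary question.

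**Working it through.** **The plan's own figure.** Inputs from Sample size: p0 = 0.30, p1 = 0.45, alpha 0.05 (taken as two-sided), power 90%. With pooled proportion 0.375:

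n = [1.960 × √(2 × 0.375 × 0.625) + 1.2816 × √(0.30 × 0.70 + 0.45 × 0.55)]² / 0.15² = 216.8, rounded up to 217.

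This matches the plan exactly, so the powered test is the uncorrected, unadjusted two-sided chi-square. With 20% loss from 260 enrolled, 260 × 0.80 = 208 per group are evaluable, with power of about 88.8%.

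**What imbalance does to the test.** The documents give no figure for selection bias, so the inputs here are assumptions. BT has no effect, controls respond at 30%, and one binary prognostic factor has prevalence a among BT takers and b among refusers. It multiplies the chance of response by rr. The spurious risk ratio is

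RR_conf = (a × rr + 1 − a) / (b × rr + 1 − b),

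and the BT cohort responds at 0.30 × RR_conf. The rejection probability comes from exact enumeration of the chi-square at 208 per group.

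| a vs b | rr | RR_conf | BT response | Rejection |
|---|---|---|---|---|
| equal | any | 1.000 | 30.0% | 5.0% |
| 60% vs 40% | 1.5 | 1.083 | 32.5% | 8.6% |
| 60% vs 40% | 2.0 | 1.143 | 34.3% | 15.6% |
| 70% vs 30% | 1.5 | 1.174 | 35.2% | 20.8% |
| 70% vs 30% | 2.0 | 1.308 | 39.2% | 50.9% |

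At 217 per group, the two rr = 2.0 rows give about 16% and 53%.

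**What adjustment costs.** If the covariates explain a share R² of cohort membership, the effective size is roughly 208 × (1 − R²) per group. Power for 30% against 45% is then:

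| R² | Effective n per group | Power |
|---|---|---|
| 0 | 208 | about 89% |
| 0.10 | 187 | about 85% |
| 0.16 | 175 | about 83% |
| 0.20 | 166 | about 81% |

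The 0.16 row corresponds to the 70% vs 30% scenario: with equal groups, the correlation between cohort and factor is 0.4, and 0.4² = 0.16.

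**The case against.** The strongest reply is that adjustment is already planned, and with some care. The confounders are agreed in advance with clinicians, univariable selection is ruled out, and robust Poisson regression is foreseen. Showing a crude comparison and then an adjusted one is ordinary in a cohort study, and the Discussion names the observational nature as a key limitation. All of this stands. A reader might infer that confounding is ignored, or that the conclusion can be freely picked once results are seen. The text supports neither. The real gap is narrower: interactions suggested by the data are allowed, and no model is named as governing. The limitation statement is general. It does not discuss selection by refusal and leaves the test unchanged.

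A second reply is that a full protocol or SAP may list the confounders. That also stands, so the missing list is not the point. The choice of an unadjusted significance test is stated in the article, and that is the point.

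A reader might also take the Discussion's remark that "different mineral waters and specific protocols will be employed at each center" as proof of confounding by centre. It is not. Controls receive no BT, so differing waters make the BT effect vary within one cohort. Centre confounds only if uptake and prognosis both differ between centres, which the article does not report. Similarly, 14% of baseline FIQ is 5.5 points at FIQ 39 (0.14 × 39) and 11.2 at FIQ 80 (0.14 × 80). That biases the comparison only if the cohorts differ in baseline FIQ.

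Finally, the scenarios are assumed and all favour BT. Selection in the other direction would hide a benefit.

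**Conclusion.** The concern holds in this form: the significance test and the 15-point relevance criterion both rest on a crude comparison of takers with refusers, while the planned adjusted analysis has no decision role and no absolute-scale estimate. This is a choice stated in the plan, and it does not fit the causal aim.

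The 5% error rate holds only if takers and refusers would respond alike without BT. The range of about 9% to 51% shows how sensitive the test is under the stated assumptions (no BT effect, one binary factor, 30% response, 208 per group). It should not be read as this study's actual error rate, because the size and direction of the bias cannot be derived from the documents. Nor does it follow that an adjusted model would restore 5%. Expectation and the reasons for refusal are not among the measures described, so some confounding may remain.

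**What to change.** Before data lock, name one adjusted model for the 15-day responder outcome as the primary analysis. Robust Poisson regression with standardisation would suit: it yields an adjusted risk ratio and an adjusted risk difference, and the latter can be set against the 15-point criterion. Fix its covariates in advance: the confounders agreed with the clinicians and, at minimum, baseline FIQ, centre, age, sex, and baseline pain, anxiety and depression. The scales are collected at baseline according to the Abstract, and centre, age and sex are known at enrolment. Drug therapy can be added only if it is recorded in analysable form; the article says only that it must be stable and that changes are reported.

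Report the chi-square and the univariable binomial model as descriptive. Label the step-by-step additions as sensitivity analyses and any interactions suggested by the data as exploratory. State in the limitations that controls are refusers and that unmeasured factors such as expectation may still confound the comparison.

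The cost is a change of wording and some precision: power of about 85%, 83% or 81% at R² of 0.10, 0.16 or 0.20, against about 89% for the crude test at 208 per group. With nine centres and several scales in the model, R² could be higher still.

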### Follow up

Following enrollment, each patient will be examined for 3 consecutive times; at baseline (T0), after 2 weeks (T1), and after 45 days (T2) (one month after the end of the cycle of the therapy for the BT Cohort) (Fig. 1). T0 and T1 visits will be carried out by the physician in the enrollment setting. The T2 visit will be carried-out by phone. The study will be considered concluded when all follow-up data for each patient will be collected.

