#### Secondary outcomes

The secondary outcomes of the study will be the differences in VAS, SF-12, STAI, and CES-D between the BT and control cohorts. These differences will be evaluated using a random effects linear regression model (RE-LRM) (Rabe-Hesketh and Skrondal 2021) 39. The response variable of such models will be the (continuous) score obtained from the scale and the predictors will be: 1) time (discrete; 0 = baseline; 1 = 15 days), 2) the cohort (discrete; 0 = control cohort and 1 = BT cohort), and 3) a time*cohort (discrete*discrete) interaction, with the random effect assigned to the patient. A Bonferroni correction will be used to correct the 95% confidence intervals and associated p-values. As already described for the BRM used for the evaluation of the primary outcome, also the RE-LRM will be expanded to a multivariable model by adding predictors (= potential confounders) determined preliminarily with the clinicians participating in the study. Interactions initially determined or suggested by the multivariable analysis may also be included among the predictors. An univariable selection of the predictors will not be carried out, but predictors will be progressively added to the model to verify the effect on the estimate of the difference in the scores for the BT and control cohort (Greenland and Pearce 2015).

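### The 15- versus 45-day responder model in the BT cohort has no patient-level term, so as written its standard error is too wide and partial loss of benefit is harder to detect

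*Protocol article*

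**What the plan says.** Persistence of efficacy over six weeks is one of the secondary aims listed at the end of the Introduction. The analysis that serves it is in the Statistical analysis plan, under Primary outcome. In the BT cohort alone, a binomial regression has as its response "the proportion of subjects with a reduction in the FIQ-Total score > 14% and time as predictor", and its purpose is given with the coding of the predictor: "time as predictor (discrete; 0 = 15 days; 1 = 45 days) to verify the stability of the change in the FIQ-Total score". The next sentence adds: "A Bonferroni correction will be used to correct the 95% confidence intervals and associated p-values".

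Three other places bear on it:

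- Follow up: every patient is assessed at baseline, at two weeks and at 45 days, so both responder values come from the same people.
- Statistical analysis plan, Secondary outcomes: the linear models for the continuous scores are specified "with the random effect assigned to the patient".
- Statistical analysis plan, Primary outcome: robust intervals are mentioned once, for a "Poisson regression model (PRM) with robust confidence intervals, to overcome the well-known problems of fitting a BRM with multiple predictors". That concerns the multivariable comparison of the two cohorts, not the time model.

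**The concern.** Each BT patient followed to 45 days contributes two rows to the time model, and the two responses should be positively correlated: they are changes from the same baseline FIQ in the same person. A binomial regression with time as its only predictor has no means of using that correlation. For a contrast within patients, ignoring positive correlation makes the standard error too large, not too small.

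In most settings a wide standard error is the safe error, because it makes a false claim of change less likely. Here the question is whether the benefit lasts, and the Discussion already expects improvement one month after treatment. An imprecise comparison makes it harder to see that part of the benefit has been lost. The estimated proportions at 15 and 45 days are not biased by this; only their comparison is affected.

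**Working it through.** **Inputs from the Sample size section.** The plan expects a FIQ decrease of "at least 14% in the 30% of the control cohort and 45% in the BT cohort", with alpha 0.05, 90% power, 217 patients per group, and 260 enrolled to allow for 20% loss.

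**Assumptions not in the documents.** Within-patient correlation rho of the two responder indicators: 0.3, 0.5 or 0.7, with 0 as the limiting case. Response at 45 days: 35% (partial loss) or 30% (complete loss, down to the control rate). Tests are two-sided. The number of BT patients with both values is taken as 260 × 0.80 = 208; results for 217 are also given.

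**The plan's own figure.** With a pooled proportion of 0.375:

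n = [1.96·sqrt(2·0.375·0.625) + 1.2816·sqrt(0.30·0.70 + 0.45·0.55)]² / 0.15² = (1.342 + 0.867)² / 0.0225 ≈ 217.

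This reproduces. The point does not concern the primary sample size. The plan gives no figure for the 15- versus 45-day comparison.

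**Standard error of the time difference, no true change (45% at both times, n = 208).** With v = p(1 − p):

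- Independence: sqrt((v1 + v2)/n) = sqrt(2·0.45·0.55/208) = 0.0488.
- Paired: sqrt((v1 + v2 − 2·rho·sqrt(v1·v2))/n) = 0.0488·sqrt(1 − rho) = 0.0408, 0.0345 or 0.0267.
- Ratio: 1/sqrt(1 − rho) = 1.20, 1.41 or 1.83. At rho = 0 it is 1.
- 95% half-width: 9.6 points under independence, against 8.0, 6.8 or 5.2 points paired.

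The true type I error of the independence model is then about 1.9%, 0.6% or below 0.1%, not 5%.

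**Power for a fall from 45% to 35% (n = 208).** Here v1 = 0.2475 and v2 = 0.2275, so the independence SE is sqrt(0.475/208) = 0.0478. The true (paired) SEs are 0.0400, 0.0338 and 0.0262.

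- Model as written: Φ[(0.10 − 1.96·0.0478)/true SE].
- Paired analysis: Φ[0.10/true SE − 1.96].

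| rho | As written | Paired |
|---|---|---|
| 0.3 | 56% | 71% |
| 0.5 | 57% | 84% |
| 0.7 | 60% | 97% |

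At rho = 0.5 the fall is missed in about 43% of studies as written and in about 16% with pairing. With 217 patients the figures are 58–63% as written, against 72%, 86% and 97%.

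**Other sizes of loss (n = 208).**

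- 45% to 40%: 13%, 10% or 5% as written, against 24%, 31% or 47% paired.
- 45% to 30%: 93%, 96% or 99% as written, against 97% to nearly 100% paired.

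**Would plain robust intervals cure it?** No. In one simulated data set of paired responses, the standard error of the log relative risk for time was 0.119 with ordinary robust variance and 0.088 with clustering by patient.

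**The case against.** The strongest objection is that silence is being read as specification. The article never says that the observations are treated as independent, and a variance option is the kind of detail that a full analysis plan could hold. This limits how firmly the point can be put: it describes what follows if the model is fitted as written. It does not remove the point. The article states the model, response, predictor, coding and multiplicity correction for this comparison, and at the same level of detail it gives a patient random effect to the secondary models.

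Several stronger readings are tempting, and the documents do not support them:

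- A reader might infer that a non-significant time effect will be declared stability. The plan speaks of verifying stability and of intervals and p-values, but states no such rule.
- A reader might infer that a lost benefit would generally go unnoticed. Complete loss to 30% is detected in more than 90% of studies even as written. The weakness concerns partial loss, and a paired analysis also misses most 5-point falls.
- A reader might call the Bonferroni correction an error and want it dropped. That assumes a family of one comparison, which the text does not define. None of the figures above includes it.
- A reader might treat the lack of a stability margin as part of the error, and half the planned effect (7.5 points) as the obvious choice. With the paired standard errors above and no true change, a 95% interval would exclude a 7.5-point fall in only about 45%, 58% or 80% of studies. A perfectly stable effect would thus fail in about 42–55% of studies at correlations of 0.3–0.5. A margin is for the sponsor to weigh.

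**Conclusion.** The point holds, as a should-fix for a secondary aim. Fitted as written, the BT-cohort time model ignores that the same patients supply both values. Its standard error is then too wide by 20%, 41% or 83% at correlations of 0.3, 0.5 or 0.7. The practical cost is lower power to see a substantial partial loss: a 10-point fall is two thirds of the planned 15-point benefit (10/15).

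The size rests on the assumed correlation, which the documents do not give, and on the chosen 10-point fall. The direction needs only that the correlation is positive. The primary comparison of cohorts at 15 days, its chi-squared test and its sample size are untouched.

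**What to change.** In the Statistical analysis plan, state that the 15- versus 45-day comparison in the BT cohort is fitted with the patient as the cluster. Suitable forms are a GEE, the binomial or Poisson model with variance clustered by patient, or McNemar's test with a paired confidence interval for the risk difference. If robust Poisson is used, say that the clustering is by patient.

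State also that persistence will be reported from the estimated change in the responder proportion and its confidence interval, and not from a non-significant p-value. Which comparisons the Bonferroni correction covers, and whether to set a stability margin, are for the sponsor to define.

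The cost is a sentence or two of text and one option in the model call. No new data or patients are needed.
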